### Collection of Medical Data

The following data were extracted from clinical trial registries: cancer diagnosis, age at diagnosis, sex, tumor location, tumor stage, study name and study arm, chemotherapy, anthracycline doses (doses of doxorubicin, per cycle and cumulatively, as defined in the study protocol for the study arm to which the patient was assigned), other cardiotoxic drugs (ie, drugs with cardiotoxic potential listed in the 2016 ESC position paper [20]), radiotherapy, irradiation field (mediastinal, lung, or left abdominal irradiation is considered a relevant cardiac risk factor [6,21]), irradiation doses of the primary tumor, relapse, and therapy (chemotherapy and irradiation) of recurrent tumor (Textbox 1).

Assessment and variables recorded.
**Cancer diagnosis and cancer treatment-related variables (obtained from study centers of the neuroblastoma trials (NB 90, NB 97, and NB 2004) and the nephroblastoma trials (SIOP 9/GPOH, SIOP 93-01/GPOH, and SIOP 2001/GPOH).**
Cancer diagnosis, tumor location, tumor stageAge at diagnosisSexStudy name and study armChemotherapy including anthracycline doses (per cycle and cumulative)Other cardiotoxic drugs (the drugs listed in the 2016 ESC position paper were considered as potentially cardiotoxic drugs)Additional radiotherapy: irradiation field, irradiation doses of the primary tumor, and the field that included the heart (mediastinal, lung, left abdominal)Length of posttherapy intervalRelapse and therapy (chemotherapy and irradiation) of the recurrent tumorComorbidities

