## Methods

### Patients

This study is part of the LESS-Anthra cross-sectional cohort study initiated by the “late effects surveillance system” (LESS). As part of this study, former cancer patients were offered a standardized cardiological examination and were surveyed about their quality of life and health status. A goal of LESS-Anthra was to establish a biobank of blood samples to allow the investigation of genetic polymorphisms that may predispose an individual to doxorubicin-induced cardiomyopathy, which is the subject of this study protocol. The study was approved by the Ethics Committee of the University of Lübeck (14-182) and the Ethics Committee of the University of Ulm (239/17). Study participants were identified through LESS, a German multicenter active surveillance consortium studying late effects of cancer treatment in children, in collaboration with the German Childhood Cancer Registry. Patients who had survived childhood cancer for 5 years or more (since diagnosis) were eligible if they (1) were diagnosed with nephroblastoma or neuroblastoma between January 1990 and December 2012, (2) were diagnosed before the age of 18, (3) were assigned to a treatment protocol that included doxorubicin (intention-to-treat), and (4) had participated in one of the nephroblastoma trials SIOP (International Society of Paediatric Oncology) 9/GPOH (German Society for Pediatric Oncology and Hematology), SIOP 93-01/GPOH, or SIOP 2001/GPOH or neuroblastoma trials NB 90, NB 97, or NB 2004. In Germany, almost all patients diagnosed with nephroblastoma or neuroblastoma between 1990 and 2012 who were willing to participate in a trial were included in one of the above-mentioned studies. Patients selected for LESS-Anthra were contacted by the German Childhood Cancer Registry, which has access to current survivor addresses. A total of 2173 patients were identified, contacted by mail, and invited to participate in the study. Those who did not respond received a reminder letter. Patients unwilling to participate in the study had the opportunity to provide us with their reason for nonparticipation via a response form. Patients were included only after they (or their parents or legal guardians, if patients were under 18 years of age) had provided informed consent. For adolescents ≥16 years, their written consent was also required.

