### Statistical Analysis

The *RARG* rs2229774, *SLC28A3* rs7853758, and *UGT1A6* rs17863783 SNPs were checked for deviations from Hardy-Weinberg equilibrium (HWE). Departure from HWE was defined as *P*-HWE <.01 (after Bonferroni correction of the nominal value of *P* set at .05) and tested by a χ^2^ test of goodness of fit between the observed and expected genotypes.

Our primary aim was to assess the value of multimarker genetic testing for *RARG* rs2229774, *UGT1A6* rs17863783, and *SLC28A3* rs7853758 for predicting doxorubicin-induced cardiovascular dysfunction. To address that aim, we considered the following 3 predictive models. Model 1 includes only clinical risk factors, such as sex, age, irradiation (mediastinal, lung, or left abdominal), the use of other cardiotoxic drugs, length of follow-up, and cumulative dose of doxorubicin. Model 2 includes only genetic profiling. For each individual, the genetic risk will be scored as suggested by the Canadian Pharmacogenomics Network for Drug Safety (CPNDS) Clinical Practice Recommendations Group [14], based on multimarker genetic testing for *RARG* rs2229774, *UGT1A6* rs17863783, and *SLC28A3* rs7853758. Patients carrying the *RARG* rs2229774 A or *UGT1A6* rs17863783 T risk variants will be classified as high genetic risk; patients carrying the *SLC28A3* rs7853758 A protective variant who do not carry *RARG* rs2229774 A or *UGT1A6* rs17863783 T alleles will be classified as low genetic risk; all other patients will be classified as moderate genetic risk (Table 3). Model 3 includes both clinical risk factors and genetic profiling. The independent contribution of each risk factor to the outcomes will be determined using multivariable logistic regression analysis. The predictive accuracy of the model will be assessed by the area under the receiver operating characteristic curve.

**Table 3 table3:** Genetic risk scoring of anthracycline-associated cardiotoxicity as suggested by the Canadian Pharmacogenomics Network for Drug Safety Clinical Practice Recommendations Group [14].

Genetic risk^a^	RARG^b^ rs2229774	UGT1A6^c^ rs17863783	SLC28A3^d^ rs7853758
High	A|G or A|A	Any genotype	Any genotype
High	Any genotype	G|T or T|T	Any genotype
Moderate	G|G	G|G	G|G
Low	G|G	G|G	A|A or A|G

^a^Risk scoring depends on the combined evaluation of three genetic markers, the polymorphisms rs2229774 in *RARG*, rs17863783 in *UGT1A6*, and rs7853758 in *SCL28A3*.

^b^RARG: retinoic acid receptor gamma.

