### Anthracycline Treatment

According to the respective protocol, and dependent on the stage and risk group, the cumulative dose of doxorubicin was 45-240 mg/m^2^ for neuroblastoma patients and 100-400 mg/m^2^ for nephroblastoma patients (Table 5).

**Table 5 table5:** Per protocol cumulative dose of doxorubicin used in the neuroblastoma (NB90, NB97, and NB 2004) and nephroblastoma (SIOP 9/GPOH, SIOP 93-01/GPOH, and SIOP 2001/GPOH) trials.

Study and study arm		Doxorubicin cumulative dose (mg/m^2^)	Single-dose, duration of IV^a^ application

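### The doxorubicin covariate is the assigned-arm dose and so leaves out relapse anthracycline; tumour type, which is closely tied to dose, is named in no model

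*Protocol article*

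**What the plan says.** All places are in the protocol article.

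- **Dose.** Under Collection of Medical Data, doxorubicin dose, per cycle and cumulative, is taken "as defined in the study protocol for the study arm to which the patient was assigned". The title of Table 5 begins "Per protocol cumulative dose of doxorubicin used in the neuroblastoma". Eligibility (Patients) likewise rests on assignment to a doxorubicin-containing protocol and is labelled intention-to-treat.
- **Recorded but not modelled.** The data list opens "The following data were extracted from clinical trial registries: cancer diagnosis, age at diagnosis, sex" and later includes "relapse, and therapy (chemotherapy and irradiation) of recurrent tumor".
- **Models.** Under Statistical Analysis, "Model 1 includes only clinical risk factors, such as sex, age, irradiation (mediastinal, lung, or left abdominal), the use of other cardiotoxic drugs", and the list ends with length of follow-up and cumulative doxorubicin dose. Model 3 adds the genetic risk group. The single-SNP models for the secondary aim adjust for the same factors, this time in a closed list. None of the lists names diagnosis or relapse treatment.
- **Use of the models.** The regression is to show what each risk factor contributes independently, and predictive accuracy is judged by the area under the ROC curve.
- **Dose by diagnosis.** Under Anthracycline Treatment, "the cumulative dose of doxorubicin was 45-240 mg/m^2^ for neuroblastoma patients and 100-400 mg/m^2^ for nephroblastoma patients".

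**The concern.** Assignment is a sound basis for comparing randomised arms. It is a weaker measure of a toxic exposure. A relapsed patient who received more anthracycline keeps the first-line value. In one arm, the NB 2004 observation group, Table 5 gives two possible doses depending on later progression, so the arm alone does not fix the dose.

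Tumour type raises a separate problem. If it is closely tied to dose and left out, the dose coefficient takes up whatever else differs between the two diagnoses. That undermines the reading of dose as an independent contributor.

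Model 1 is also the yardstick for the primary aim, since the value of genotyping is judged against what clinical factors already predict. If the yardstick is weaker than the recorded data allow, the markers may look more useful than they are.

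**Working it through.** **1. The article's own ranges.** Arm doses in Table 5 (mg/m²), with the 45 and 180 of the NB 2004 observation group counted separately:

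- Neuroblastoma, 9 values: 120, 240, 60, 120, 180, 45, 180, 180, 180. Sum 1,305, mean 145, range 45 to 240.
- Nephroblastoma, 10 values: 250, 400, 100, 250, 300, 400, 250, 250, 300, 300. Sum 2,800, mean 280, range 100 to 400.

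Both ranges agree with the text. No neuroblastoma value exceeds 240; 9 of the 10 nephroblastoma values do.

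**2. Share of dose variance explained by tumour type, arms equally weighted.**

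- Between-tumour sum of squares: (9 × 10 / 19) × (280 − 145)² = 86,329.
- Within-tumour: 32,400 (neuroblastoma) + 66,000 (nephroblastoma) = 98,400.
- Total: 184,729. Share: 86,329 / 184,729 = 0.467.

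With the participant mix of 284 neuroblastoma to 373 nephroblastoma (Recruitment), and arms still equal within each diagnosis:

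- Between: 0.432 × 0.568 × 135² ≈ 4,473.
- Within: 0.432 × 3,600 + 0.568 × 6,600 ≈ 5,303.
- Share: 4,473 / 9,776 ≈ 0.46.

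Patient numbers per arm are not given, so neither figure is the patient-level value.

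**3. What omission could do (simulation).** Every effect size here is an assumption: dose OR 1.5 per 100 mg/m²; genetic OR 2 per risk category; nephroblastoma-versus-neuroblastoma OR 0.5, 1 or 2; relapse in 0 to 20%, adding the equivalent of 150 mg/m². The Table 5 doses, the 284:373 mix and the Table 7 risk-group shares come from the article. *Planned* uses assigned dose only. *Fuller* uses true exposure plus diagnosis.

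| Relapse | Diagnosis OR | Dose OR, planned / fuller | Model 1 AUC, planned / fuller | Genetic AUC gain, planned / fuller |
|---|---|---|---|---|
| 0 | 0.5 | 1.18 / 1.48 | 0.540 / 0.577 | 0.078 / 0.061 |
| 0 | 1 | 1.49 / 1.48 | 0.608 / 0.608 | 0.047 / 0.047 |
| 0 | 2 | 1.84 / 1.48 | 0.668 / 0.674 | 0.031 / 0.033 |
| 20% | 0.5 | 1.18 / 1.49 | 0.538 / 0.606 | 0.081 / 0.050 |
| 20% | 1 | 1.47 / 1.47 | 0.605 / 0.624 | 0.050 / 0.044 |
| 20% | 2 | 1.85 / 1.49 | 0.668 / 0.687 | 0.031 / 0.030 |

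Over all settings, including 10% relapse:

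- The dose OR runs from 1.17 to 1.85 as planned, against 1.47 to 1.49 in the fuller model.
- Model 1's AUC is 0.00 to 0.07 lower as planned.
- The genetic OR is 1.97 to 2.04 as planned and 1.98 to 2.05 in the fuller model.

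**4. Reading the table.** Omitting diagnosis moves the dose coefficient in either direction. Relapse of this kind, independent of arm, leaves the dose slope nearly unchanged and costs discrimination (0.605 against 0.624 at 20% relapse and diagnosis OR 1). The genetic gain is clearly inflated only where nephroblastoma is assumed protective.

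**5. Sample size.** The stated 33 cases and 99 controls do not depend on this point, and they reproduce. Carrier frequency in controls is 1 − (1 − 0.064)² = 0.124. In cases at OR 4.7 it is 0.399. A two-sided 5% test with continuity correction, 80% power and 3:1 controls needs 29 cases; 29 / 0.9 = 32.2, rounded up to 33.

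**The case against.** The other side has four good arguments.

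*The lists are not clearly closed to these factors.* Model 1's list is introduced as examples. Irradiation and other cardiotoxic drugs are not restricted to first-line treatment, so relapse irradiation and non-anthracycline relapse drugs may already count. This stands: a reader might infer that the models ignore relapse treatment altogether, but the text shows that only for relapse anthracycline. For the rest it is ambiguous, because irradiation dose is tied to the primary tumour and relapse therapy is listed separately. The SNP list is closed and has the same gaps.

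*The aim is prediction, not the dose slope.* When diagnosis and dose push risk the same way, dose stands in for diagnosis and Model 1 loses little. This largely stands for the AUC comparison. It does not answer the plan's promise of an independent contribution for each factor.

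*The inflated genetic gain depends on assumptions.* A second simulation, with relapse adding 200 mg/m², gave these gains, planned against fuller: 0.048–0.049 against 0.040–0.048 at diagnosis OR 1; 0.032–0.034 against 0.029–0.036 at OR 2; 0.080–0.082 against 0.044–0.061 at OR 0.5. This stands. A reader might infer that the plan biases the primary genetic result; the documents do not support that.

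*The assigned-dose definition is open, and details may sit in an analysis plan.* The definition is indeed stated plainly. A reader might also want patients who never received doxorubicin removed, but nothing in the article shows that receipt was recorded. The covariates, however, are named twice in the article, and the gap lies in that naming.

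**Conclusion.** The point holds in a limited form. As written, relapse anthracycline is outside the dose covariate, and tumour type, which accounts for about 46 to 47% of dose variance under equal arm weights within diagnosis, is in none of the named lists. The dose coefficient cannot be read as independent of diagnosis, and Model 1's AUC may be somewhat too low.

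The genetic odds ratio is little affected, provided genotype is unrelated to treatment and diagnosis. Whether the genetic AUC gain is overstated, and by how much, cannot be determined: the article gives no relapse rate, relapse or received doses, or diagnosis effect. The simulated values show direction and plausible range under stated assumptions; they are not estimates for this cohort. The primary genetic comparison is not invalidated. This is an inexpensive improvement to the benchmark, worth making while analyses are incomplete and the database is still open.

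**What to change.** Under Statistical Analysis, for Models 1 and 3 and the single-SNP models:

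1. Add tumour diagnosis and a relapse-treatment indicator as covariates.
2. State that the irradiation and other-cardiotoxic-drug covariates include relapse therapy.
3. Add relapse anthracycline to the cumulative dose where it is recorded. Otherwise call the covariate protocol-assigned dose.
4. Repeat the primary analysis without relapsed patients.

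**Cost.** Diagnosis and relapse therapy are already recorded, and the planned 33 cases and 99 controls do not change. The models gain one or two parameters. Model 3 as named has about 8 (six clinical terms, if irradiation is one term, and two for the genetic group). At 33 cases that is 33 / 8 ≈ 4.1 cases per parameter, falling to 33 / 10 = 3.3, so penalised estimation may be needed if cases are near that number; the actual number is not given. Adding diagnosis also makes the dose coefficient less precise: with 47% shared variance and other covariates ignored, its standard error grows by about √(1 / (1 − 0.467)) = 1.37.

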**Results of interview and clinical and physical examination (obtained at presentation to cardiologist).**
Anthropometry: weight (kg) and height (cm)
**Systolic and diastolic blood pressure (mmHg) according to current guidelines for conventional office blood pressure measurement (ie, patients should be seated comfortably 5 min before measurements, at least 3 measurements 1-2 min apart, blood pressure is recorded as the average of the last 2 readings)**
Heart rate (beats per minute)ECG findings: Cardiac arrhythmia with type (bradycardia, tachycardia, ventricular, or supraventricular); heart block findings with type (atrioventricular block with degree, complete right bundle branch block, or complete left bundle branch block); QTc prolongation (ms); signs of cardiac hypertrophy with type (right heart hypertrophy or left ventricular hypertrophy); other ECG pathologiesFindings on clinical examination (edema, dyspnea at rest, cyanosis, hepatosplenomegaly, jugular venous congestion, or arrhythmia by auscultation).Diagnoses made by the cardiologist: Heart failure (right heart failure, left heart failure, or global heart failure; NYHA stage); cardiomyopathy (dilated, hypertrophic, restrictive, or other); arterial hypertension (primary hypertension or secondary hypertension); cardiac arrhythmia (type)The patient's expressed subjective resilience in everyday life (5 level rating: very good, good, average, poor, and very poor).The patient's expressed subjective ability to engage in sports activities (2 level rating: sports activity possible/not possible).
**Echocardiographic parameters (echocardiographic evaluation center)**
Left ventricular size: Linear measurements; volume measurements; left ventricular mass calculationsLeft ventricular function assessment: Global systolic function parameters (fractional shortening or ejection fraction); global myocardial function assessed by Doppler-derived Tei indexLeft and right atrium area and volume measurements

### Cardiologic Examination

Cardiologists were asked to perform echocardiographic examinations according to the instructions provided. Table 1 shows the minimal digital acquisition protocol for transthoracic echocardiography. The echocardiographic recordings were centrally evaluated by a pediatric cardiologist in a standardized way and blinded for treatment exposure and genetic test results to minimize interinvestigator variability. In rare cases, in which parts of the echocardiography recordings were of insufficient quality, the corresponding data points were treated as missing values.

Additional information, such as clinical examination findings, weight, height, heart rate, blood pressure, and physical performance of the patient, was collected using a questionnaire (Table 1). This questionnaire was completed by the cardiologist and sent to the cardiological evaluation center.

**Table 1 table1:** Minimal digital acquisition protocol for transthoracic echocardiography.

View		Data type
**Long-axis view, M-mode**		Still frame
	At the level of the tip of the posterior mitral valve leaflet (basal myocardial segment)	
**Four-chamber view (2D)**		Loop
	Left atrium and left ventricle, endocardium and myocardium, with mitral valve, left atrium shown with maximum area	
	Right atrium and right ventricle, endocardium and myocardium, with tricuspid valve	
**Short-axis view (2D)**		Loop
	Round section through left ventricle at mitral valve level, right ventricle incised	
**Two-chamber view (2D)**		Loop
	Left ventricle, endocardium and myocardium	
**Three-chamber view (2D)**		Loop
	Left atrium, left ventricle and aorta, endocardium and myocardium, with mitral valve, left atrium shown with maximum area	
**Pulsed-wave or continuous-wave Doppler**		Spectral doppler, still frame
	Mitral valve	
	Tricuspid valve	
	Aortic valve	
	Pulmonary valve	

### Outcomes

The primary endpoint was cardiac dysfunction, as diagnosed by the cardiologist or revealed by a central assessment of transthoracic echocardiography. Cardiac dysfunction is presumed when at least one of the following criteria is true:

Diagnosis by the cardiologist of heart failure or cardiomyopathy reported in the questionnaire.Left ventricular ejection fraction reduced to <50%.Shortening fraction reduced to <25%.Relative wall thickness reduced to <0.22.Percentage systolic thickening of the interventricular septum and left ventricular (LV) posterior wall reduced to <33%.LV Tei index (myocardial performance index) >0.40.Right atrial volume at end systole/body surface area >30 ml/m^2^.

The secondary endpoint is cardiovascular dysfunction, defined as the composite of arterial hypertension (diagnosed by the cardiologist and reported in the questionnaire or current blood pressure measured during the visit ≥140 mmHg systolic or ≥90 mmHg diastolic), cardiac arrhythmia (diagnosed by the cardiologist and reported in the questionnaire), and cardiac dysfunction (as defined above).

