**Figure 1 figure1:**
[figure not shown]
Flowchart of patients’ inclusion or exclusion.

**Table 4 table4:** Comparison of baseline characteristics of participants and nonparticipants of the LESS-Anthra study.

	Patients invited for participation (n=2158)	Nonresponders, no consent, or refusal (n=1499)	Participants (n=657)
Age at diagnosis (years), median (range)	2.0 (0-17)	2.0 (0-17)	2.0 (0-17)
Follow-up time (years), median (range)	14.0 (5-27)	15.0 (5-27)	13.0 (5-27)
Proportion of male to female patients	1.0	0.9	1.2
Proportion of nephroblastoma to neuroblastoma patients	1.3	1.3	1.3

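### The measured hypertension criterion applies one 140/90 mmHg cut-off from about age 5 to adulthood, so ascertainment of this part of the secondary composite depends on age

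*Protocol article*

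**What the plan says.** The Outcomes section of the protocol article states: "The secondary endpoint is cardiovascular dysfunction, defined as the composite of arterial hypertension", together with cardiac arrhythmia and cardiac dysfunction. Hypertension can be met in two ways, joined by 'or': the cardiologist's diagnosis on the questionnaire, or "current blood pressure measured during the visit ≥140 mmHg systolic or ≥90 mmHg diastolic". The second route carries no condition on age, sex or height. Textbox 1 refers to current guidelines for how blood pressure is taken (seated rest, repeated readings, averaging), but gives no reference values by age.

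The cohort includes children. Under Patients, "Patients who had survived childhood cancer for 5 years or more (since diagnosis) were eligible", diagnosis had to fall before age 18, and parental consent is provided for those still under 18. Table 4 gives participants a median age at diagnosis of 2.0 years (range 0-17) and a median follow-up of 13.0 years (range 5-27).

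The prevalence of cardiovascular dysfunction is a declared secondary objective (Introduction; also the Abstract's Objective).

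**The concern.** Blood pressure normally rises with age and body size through childhood. That is general knowledge rather than document text, but it decides how a single absolute limit behaves here. A limit that an adult can reach on one visit is far outside the usual range of a six-year-old. The measured route is thus close to inactive in the youngest participants and active in the oldest. The same section indexes right atrial volume to body surface area, so body size is allowed for in one criterion and not in this one.

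What is at stake is mainly the prevalence estimate. If raised pressure in minors is picked up less completely than in adults, the hypertension component is under-counted in the younger part of the cohort. A higher rate at older ages or longer follow-up would then be partly a product of the definition.

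**Working it through.** The article reports neither age at examination nor an expected hypertension rate, so there is no stated figure to reproduce. The check derives the age range and then asks how the cut-off behaves across it.

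**1. Age at examination (inputs: Table 4, participants).** Age at examination = age at diagnosis + follow-up time.
- Youngest possible: 0 + 5 = about 5 years.
- Largest possible sum: 17 + 27 = 44 years (two separate maxima, perhaps not the same person).
- Sum of medians: 2 + 13 = 15 years. A sum of medians is not the median of the sum, so this is a guide only.
- Firm lower bound: nobody's age can be below their follow-up time, so the median age is at least 13.

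**2. Plausible median and share of minors (assumed shapes).** Age at diagnosis was simulated under three shapes with median about 2 and all ages below 18. Follow-up was piecewise uniform with median 13 and range 5-27. The two were taken as independent, fully positively dependent and fully negatively dependent. Across the nine combinations:
- the median age at examination was 15.0 to 16.6 years;
- 56% to 63% were under 18, and 47% to 54% under 16.

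The examination could take place up to 12 months after agreement to participate. If follow-up was counted to an earlier date, ages shift up by at most about a year, and the share of minors then lies between those two sets of figures. Roughly half or more are minors either way.

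**3. Behaviour of the systolic limit (assumed means and SDs).** P(SBP ≥ 140) = 1 − Φ((140 − mean)/SD). The range moves the mean by ±5 mmHg.

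| Age | Mean / SD (assumed) | z at mean | P at mean | Range |
|---|---|---|---|---|
| about 6 | 95 / 9 | 45/9 = 5.00 | 0.00000 | 0.00000 throughout |
| about 10 | 102 / 10 | 38/10 = 3.80 | 0.00007 | 0.00001-0.0005 |
| about 15 | 113 / 11 | 27/11 = 2.45 | 0.007 | 0.002-0.023 |
| about 25 | 120 / 12 | 20/12 = 1.67 | 0.048 | 0.019-0.106 |

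The diastolic limit was not modelled. The pattern is the point: practically nothing flagged at 6 to 10 years, a little at 15, several per cent in young adults.

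**4. Illustrative shortfall.** Understatement of the hypertension component = (share of minors) × (share of minors whose pressure is raised for age, who are below 140/90 and who are not diagnosed by the cardiologist). The second factor is unknown; 2% to 10% is assumed.
- Low end: 0.56 × 2% = 1.1 points.
- High end: 0.63 × 10% = 6.3 points.

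For the composite, multiply by (1 − q), where q is the share of those missed who already qualify through arrhythmia or cardiac dysfunction. The documents give no value for q, so the composite shortfall is no larger than that of the component and probably smaller.

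**The case against.** The strongest reply is that the fixed cut-off is not the only paediatric criterion. The cardiologist examines the participant, records height, weight and blood pressure, and can report hypertension at any reading. This stands, and it means that hypertension in a child is not automatically missed. But the protocol gives no criteria for that diagnosis, and participants could choose their own cardiologist. In the young, ascertainment rests largely on individual judgement; in adults an objective reading also suffices. The asymmetry is reduced, not removed.

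The analyses also include age and length of follow-up (Model 1, Model 3 and the adjusted SNP analyses). That can absorb part of the gradient in a regression. It does not restore missed cases or correct a prevalence.

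A reader might be tempted to infer three stronger things that the documents do not support.

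- **That the primary aim is compromised.** The Introduction and Statistical Analysis word the primary aim in terms of cardiovascular dysfunction. The Outcomes section, however, names cardiac dysfunction as the primary endpoint, and none of its criteria concerns blood pressure. The difference in wording is a separate matter and should not lend weight to this one.
- **That the rule inflates the coefficients and AUC of the models.** No coefficient or AUC has been computed. Age and follow-up are in both Model 1 and Model 3, so any such effect largely cancels when asking what genetic profiling adds. Nothing in the documents links genotype to age at examination, and cardiologists did not know the genotypes.
- **That cardiovascular dysfunction is understated by several points.** The illustrative figures apply at most to hypertension, and they rest on an assumed rate of missed cases.

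**Conclusion.** The point holds for one component of the secondary composite. The Outcomes section fixes a single measured limit for a cohort that runs from about age 5 to adulthood and has a median age at examination of at least 13. As written, the measured route works very differently at the two ends of that range. The likely direction is an under-count of hypertension in minors, with a smaller, unknown effect on the prevalence of cardiovascular dysfunction. The size cannot be derived from the documents; the 1 to 6 points for the hypertension component are illustration only.

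This rests on general knowledge that blood pressure rises through childhood, on ages derived from Table 4, and on the diagnosis route not catching every child with raised pressure. Some true hypertension also increases with age, so only part of an observed gradient would be artefact. The change is worth making because prevalence is a declared objective that covariate adjustment cannot repair.

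**What to change.** Amend the definition in Outcomes, for outcome classification only. For participants under 18 at examination, code measured blood pressure against an age-, sex- and height-specific paediatric reference that the investigators choose and name before the database is closed. Keep the fixed cut-off for adults and the diagnosis route for all. Report the prevalence of hypertension and of cardiovascular dysfunction separately for minors and adults. It would also help to show how many hypertension cases came from each route in each age group.

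The cost is a sentence or two in Outcomes and a recoding step. Sex, height and blood pressure are already recorded, age at examination can be derived, and the article's Data Collection section under Results says that checks before database closure are still under way. No new data are needed.
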